# Effects of Astragalus injection and Salvia Miltiorrhiza injection on serum inflammatory markers in patients with stable coronary heart disease: a randomized controlled trial protocol

**DOI:** 10.1186/s13063-020-4109-6

**Published:** 2020-03-17

**Keywords:** Stable coronary heart disease, Astragalus injection, *Salvia miltiorrhiza* injection, Randomized controlled trial

## Abstract

**Background:**

Coronary heart disease (CHD) is a clinical syndrome caused by coronary atherosclerosis (AS) or functional changes in coronary arteries. We have previously reported that astragaloside IV (in astragalus) and tanshinone IIA (in *Salvia miltiorrhiza*) improve myocardial ischemic injury.

**Methods:**

This study will employ the randomized, blinded, prospective, single-center experiments approach. Briefly, a total of 160 eligible patients will be equally randomized into three treatment groups and placebo control groups. Patients will receive appropriate treatments every 24 h for seven days after enrollment and followed up for 28 days. The main evaluation indicators will be cell count, serum high-sensitivity C-reactive protein (hs-CRP) level, monocyte chemoattractant protein 1 (MCP-1), interleukin-6 (IL-6), interleukin-1β (IL-1β), interleukin-8 (IL-8), interleukin-18 (IL-18), interleukin-10 (IL-10), tumor necrosis factor (TNF)-α, oxidized low density lipoprotein (OX-LDL), angina grade, and Traditional Chinese Medicine (TCM) symptom changes scale. Secondary indicators to be evaluated will include B-type natriuretic peptide (BNP) levels, troponin (cTn), muscle enzyme isoenzyme (CK-MB), heart-type fatty acid binding protein (H-FABP), liver and renal functions, as well as blood coagulation. Close monitoring of adverse events during the trial will also be conducted.

**Discussion:**

This randomized controlled trial of Chinese herbal extracts for the treatment of coronary heart disease will generate results that are expected to provide valuable clinical evidence to inform future development of therapies towards management of CHD.

**Trial registration:**

China Clinical Trial Registration Center, ChiCTR1900021590. Registered on 28 February 2019.

## Background

Coronary heart disease (CHD) is a clinical syndrome caused by coronary atherosclerosis (AS) or functional changes in the coronary arteries. This condition results in the narrowing of the vascular lumen and insufficient blood supply to the coronary arteries, thereby increasing the load on the heart and leads to acute and temporary ischemia as well as hypoxia of the myocardium. Coronary AS is a serious disease that endangers human health. In recent years, studies have found that AS is not only a simple lipid deposit, but also an inflammatory disease. Local or systemic inflammatory response plays an important role in the development of AS and its related complications [1]. Therefore, anti-inflammatory therapies have been proposed as the ideal means of treating AS. In fact, many studies have shown that statins, angiotensin-converting enzyme inhibitors (ACEIs), antiplatelet agents, calcium channel blockers, and other drugs have certain anti-inflammatory properties that can be exploited to manage the condition [2].

Inflammatory factors, endogenous peptides mainly produced by immune cells with strong biological effects, are known to be indicators of inflammatory responses. Specifically, they mediate a variety of immune responses, which are closely related to occurrence and development of coronary heart disease [3]. Studies have shown that serum high-sensitivity C-reactive protein (hs-CRP) is one of the markers of inflammation, helping to indicate an increased risk of vascular events, and aid prognosis and risk stratification. Consequently, this marker is a potential target for the treatment of AS and its complications [4]. Numerous reports have demonstrated a close relationship between level of hs-CRP, monocyte chemoattractant protein 1 (MCP-1), interleukin-6 (IL-6), interleukin-8 (IL-8), and tumor necrosis factor (TNF)-α with pathogenesis of coronary heart disease [5, 6]. Since inflammatory factors are involved in the occurrence and development of CHD, exploring the relationship between various inflammatory factors and coronary heart disease can provide a deeper understanding of the pathogenesis of this disease. In addition, quantification of various inflammatory factors can help to dynamically understand a patient’s condition, while assessing the effects of treatment can guide clinical practice [7].

Coronary heart disease is categorized as “chest pain” and “heartache” in Traditional Chinese Medicine (TCM), which plays an important role in its diagnosis and treatment. In particular, the “Yiqihuoxue” is the most widely used method for managing the condition [8]. Among the components therein, astragalus and Salvia are the most commonly used compatibility drugs. In our previous studies, we focused on investigating the roles of TCM in CHD [9–12]. In particular, it is evident that astragalus membranaceus, the main component of astragalus membranaceus, and tanshinone IIA, the main component of *Salvia miltiorrhiza*, can effectively improve myocardial ischemic injury [13]. Functionally, the mechanism of action of the Salvia miltiorrhiza is related to inhibition of cell inflammatory reaction and apop-tosis in myocardial ischemic injury [14].

Based on the above understanding, we hypothesize, from a clinical perspective, that individual astragalus and *Salvia miltiorrhiza* injections, or a combination of the two, have certain anti-inflammatory properties and could play a role in the treatment of CHD. We therefore aim to explore the effects of *Salvia miltiorrhiza* treatment on stable CHD and provide the basis for its clinical application.

## Methods/design

### Study design and settings

The present study will be set up using randomly blinded and single-center experiments. We will recruit 160 patients who meet the eligibility criteria at the Guangdong Provincial Hospital of Traditional Chinese Medicine. Subsequently, the participants will be divided into four equal groups: three groups with treatment (treatment group A will receive conventional drugs plus astragalus injection treatment, group B will receive conventional drugs plus *Salvia miltiorrhiza* injection, and group C will receive conventional drugs plus *Salvia miltiorrhiza* and astragalus injections) and the control group will receive conventional drugs plus 0.9% NaCl injection. The study design is as illustrated in Fig. 1.

**Fig. 1 Fig1:**
[figure not shown]
Trial flow chart

### Objectives

This study intends to explore the effects of astragalus and *Salvia miltiorrhiza* injections as well as a synergistic treatment (of the two components) on stable CHD from the anti-inflammatory advantage and provide the basis for its clinical application.

### Research standard

All patients enrolled in the study should meet the following diagnostic and inclusion criteria. In addition, the patients will sign an informed consent form (ICF) before the study.

### Diagnostic criteria

The criteria for diagnosis of CHD will be as follows: (1) coronary angiography or coronary computed tomography (CT) examination confirmed at least one major branch lumen diameter stenosis of > 50%, clinical with or without angina, heart failure, arrhythmia, sudden or death recovery; (2) clear evidence of ST-segment elevation or non-ST-segment elevation myocardial infarction; and (3) a history of percutaneous coronary intervention (PCI) and/or coronary artery bypass grafting (CABG).

Clinical diagnostic criteria for chronic stable angina will be as described [15]: chronic stable angina is a condition in which a patient’s degree, frequency, nature, and predisposing factors of angina pectoris have not changed significantly within one month. The criteria will be as follows; (1) pain area: the typical part is the posterior sternum or left front chest, which can be radiated to the neck, pharynx, jaw, upper abdomen, shoulder and back, left arm, and left finger; (2) nature of pain: patients that often show symptoms of tightness, squeezing, pressure, burning, chest, chest tightness or suffocation, heavy feeling, subjective feelings vary widely, and some manifest as fatigue and shortness of breath; (3) duration: a paroxysmal episode lasting a few minutes, generally no more than 10 min; and (4) predisposing factors and mitigation methods: patients whose seizures are related to labor or emotional excitement can be relieved after stopping to rest and sublingual nitroglycerin can quickly relieve symptoms within 2–5 min.

### Inclusion criteria

The inclusion criteria are as follows: (1) patients meet the stable coronary atherosclerotic heart disease (SCAD) diagnostic criteria; (2) their medical history is > 3 months, frequency of angina pectoris is ≥ 3 times in the past one week, and the severity of angina pectoris is grade I–II/I–III; (3) patient’s age is 18–75 years; (4) patients with SCAD treated with any combination of cardiac-related drugs for > 3 months before enrollment, including atorvastatin, aspirin, angiotensin-II receptor blockers (ARBs), ACEIs, and beta-receptor blockers; and (5) patients signed the ICF.

### Exclusion criteria

The exclusion criteria are as follows: (1) patients with acute coronary syndrome (ACS) who are asymptomatic or have stable symptoms after stabilization; (2) patients requiring revascularization, including myocardial infarction, left ventricular dysfunction, multivessel disease, and/or large-scale myocardial ischemia (ischemic area > 10%), left main disease; (3) patients with chronic refractory angina pectoris; (4) patients with chronic kidney disease and severe heart, lung, liver, and other important organ dysfunction; serious primary diseases such as hematopoietic system and endocrine system, malignant tumor, gastrointestinal bleeding, gastric ulcer, and bleeding tendency are not expected complete the tester; (5) patients with severe and uncontrolled hypertension (systolic blood pressure ≥ 180 mmHg or diastolic blood pressure ≥ 110 mmHg); (6) those with severe arrhythmia (ventricular dichotomy, ventricular tachycardia, ventricular fibrillation, third degree atrioventricular block, arrest, severe sinus bradycardia, sick sinus syndrome, re-entrant supraventricular tachycardia, arrhythmia causing hemodynamic changes); (7) patients who participate in other clinical trials or are taking other proprietary Chinese medicines within one month; (8) pregnancy, or preparation for pregnancy, and lactating women; and (9) people with mental, psychological, and other problems that cannot be matched with the completion of the research.

### Loss to follow-up

Patients who are enrolling but have not completed clinical observations, including those withdrawing by themselves, losing their follow-up, poor compliance, or being withdrawn by a physician. If there are valid data in the case of shedding, the result of the last major efficacy index will be converted to the final result for statistical analysis.

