### Sample size

This study will use a parallel design of randomized controlled trials and hs-CRP as the main effect index. Conventional Western medicine treatment can reduce hs-CRP by 32%, according to clinical conditions, and it is estimated that Chinese medicine can reduce hs-CRP by 52%. The set α = 0.025, β = 0.2, superiority limit value δ = 20%, and the sample size of each group will be calculated as 30 cases [16, 17]. Considering the loss of follow-up, 40 patients with stable coronary heart disease and 160 with four combinations will be selected.

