### Statistical analysis

Statistical analysis will be performed using SPSS 19.0 statistical software. Measured data will be described using means and standard deviation of the mean, while count data will be by the number of cases in percentages. First, a baseline analysis of the demographic characteristics in the four groups of selected cases will be conducted to investigate the balance and comparability across groups. Then, the effectiveness and safety indices will be compared across the four groups. The comparison of iso-quantitative data between the experimental and the control group will be performed using a student *t*-test of two-sample comparison for group design, while the comparison of the two classification indicators such as gender will be performed using the Cochran-Mantel-Haenszel χ^2^ test or Fisher’s exact probability method. The missing supplementary data will be adjusted using imputation methods. To validate ineffectiveness among the groups, we will perform a rank sum test of the two-sample comparison in the groups. All statistical tests will be two-sided with *p* ≤ 0.05 to be used for statistical significance.

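### The protocol fixes last observation carried forward for dropouts on the main efficacy index; this can shift the hs-CRP contrast in either direction and is not reconciled with the imputation sentence in the analysis section

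*Protocol article*

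**What the plan says.** The Loss to follow-up section of the protocol article covers enrolled patients who did not complete the clinical observations, "including those withdrawing by themselves, losing their follow-up, poor compliance, or being withdrawn by a physician". For those with usable data it sets a rule: "the result of the last major efficacy index will be converted to the final result for statistical analysis". In effect this is last observation carried forward.

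The Sample size section takes "hs-CRP as the main effect index" and assumes a fall of 32% with conventional treatment and 52% with the Chinese medicine. It raises the group size from 30 to 40 to allow for loss.

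The Statistical analysis section has one sentence on missing data: "The missing supplementary data will be adjusted using imputation methods". It names no method and does not refer to the carry-forward rule.

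The Blinding section expects double-blinding to be difficult because of the colour of the injections. Treatment lasts seven days. Records are daily on days 1 to 7, with a follow-up on day 28.

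**The concern.** Carry-forward is neutral on average only if the last value seen already stands where the final value would have stood. The plan assumes hs-CRP falls in every arm, and nothing in the article says how fast. A patient who leaves early would contribute too small a fall. The error per dropout is larger in the arm with the larger fall, and the total error depends on how many patients each arm loses.

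Unequal loss is plausible here. Staff who can see which infusion is running may also withdraw patients. Masked outcome assessors do not protect against that.

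The wording adds to the exposure. Poor compliance and physician withdrawal are about treatment, not about whether blood can be drawn. Listing them under loss to follow-up invites sites to stop measuring such patients, and the carried value then stands in for one that could have been obtained.

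Finally, carried values enter the two-sample tests as if observed at the final time, so the analysis takes no account of the uncertainty about what the final value would have been.

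**Working it through.** **The plan's own figure.** The step from 30 to 40 per group corresponds to 30 / (1 − 0.25) = 40, an allowance of 10/40 = 25%. No loss rate is stated, so 25% is only implied.

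**Inputs from the Sample size section.** Fall of 32% on control and 52% on active treatment, read as mean percentage reductions; planned contrast 52 − 32 = 20 points.

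**Assumptions.** *d* is the share of an arm whose value is carried forward. *f* is the fraction of the final fall already reached at the last value, from 0 (still at baseline) to 1 (fall complete). The documents give neither. The 10% rate and the split between arms are chosen for illustration.

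**Formula.** Expected arm mean under carry-forward = true fall × [1 − d(1 − f)]. The contrast is therefore

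20 − (1 − f) × (52 × d_active − 32 × d_control).

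**Results with a true contrast of 20 points.**

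| Loss, active / control | f = 0 | f = 0.5 | f = 1 |
|---|---|---|---|
| 25% / 25% | 39.0 − 24.0 = 15.0 | 45.5 − 28.0 = 17.5 | 20.0 |
| 25% / 10% | 39.0 − 28.8 = 10.2 | 45.5 − 30.4 = 15.1 | 20.0 |
| 10% / 25% | 46.8 − 24.0 = 22.8 | 49.4 − 28.0 = 21.4 | 20.0 |

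**Results with no true effect** (32% fall in both arms), 25% active and 10% control loss:

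- f = 0: 24.0 − 28.8 = −4.8 points
- f = 0.5: 28.0 − 30.4 = −2.4 points
- f = 1: 0

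The spurious difference counts against the arm that loses more patients. Swapping the loss rates swaps the sign.

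**Direction.** For f below 1 the planned contrast shrinks when 52 × d_active exceeds 32 × d_control, and grows when active loss is less than 32/52 ≈ 0.62 of control loss. Equal loss therefore attenuates.

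**The two missing-data sentences side by side.** Loss to follow-up names a method (last value) for a defined group (dropouts with usable data). Statistical analysis names no method and no group. Carry-forward is itself a form of imputation, so both can be true together. What the text does not settle is whether a second method applies, and to which data.

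**The case against.** The strongest reply is that the figures depend on inputs the plan does not give: loss by arm, the time course of hs-CRP, and the primary time point. Treatment is short and apparently given in hospital, so most loss may fall after day 7. An analysis at day 7 would then carry little forward, and one at day 28 would carry end-of-treatment values rather than baseline ones. The sampling schedule may be in Fig. 2, which is not shown. This stands as a limit on size, and it is why ranges are given. It does not rescue the rule, because nothing in the article shows that hs-CRP has settled by the last value.

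It is also fair that withdrawal for reactions to the active infusions would, on this arithmetic, work against the active arm. Inflation needs clearly higher loss on control.

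Three stronger readings are tempting, but the documents do not support them:

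- *The two sections contradict each other.* They do not. The later sentence is unspecific and could include carry-forward, or could refer to isolated missing items.
- *Dropouts without usable data are excluded.* The Loss to follow-up section is silent about them, and the imputation sentence could cover them.
- *Later measured values of poor compliers are overwritten.* The section is confined to patients who did not complete observations. A poor complier who completes them falls outside it on a natural reading. The wording creates a risk; it does not state such a rule.

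**Conclusion.** The point holds as a badly chosen rule that the protocol itself fixes, not as a missing detail. Carry-forward can bias the hs-CRP contrast, but bias is not certain and has no fixed direction.

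Under the assumed loss rates, and with between none and all of the fall reached at the last value, the distortion of the 20-point contrast runs from a loss of 9.8 points to a gain of 2.8. With no true effect it is up to 4.8 points against the arm with more loss. At half the fall these become 4.9, 1.4 and 2.4; at a plateau they vanish. If hs-CRP were to rise again after treatment and the final result were day 28, the signs would reverse; that case lies outside the ranges.

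No size is put on the understatement of uncertainty, because the article gives no standard deviation and no correlation between days. Severity: should fix, before the data are unblinded.

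**What to change.** 1. In Loss to follow-up, remove carry-forward as the primary rule. Separate stopping or poorly following treatment from being lost to observation.
2. State that the scheduled measurements continue in every randomised patient who still consents, whatever their compliance or treatment status, and that the analysis is by randomised group.
3. Make the primary analysis of hs-CRP a likelihood-based repeated-measures model on all available values, or multiple imputation within arm. Either is acceptable; name one.
4. Keep carry-forward at most as a sensitivity analysis. Both primary options assume data missing at random, which withdrawal for reactions could violate, so add a sensitivity analysis that relaxes this assumption.
5. Make Loss to follow-up and Statistical analysis state the same rule, including what is done for dropouts without usable data.

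The cost is revised wording, some extra analysis work, and continued sampling of patients who might otherwise have been let go. The text already schedules days 1 to 7 and day 28, so no new visit is needed; whether hs-CRP is drawn at each cannot be checked without Fig. 2.

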### Suspension criteria

The trial will be suspended in case of the following: (1) serious adverse reactions occurred during the testing; and (2) the trial finds that the clinical trial program has major errors, or the program is good, but serious deviations occur during implementation, and it is difficult to evaluate the efficacy of the drug.

### Sample size

This study will use a parallel design of randomized controlled trials and hs-CRP as the main effect index. Conventional Western medicine treatment can reduce hs-CRP by 32%, according to clinical conditions, and it is estimated that Chinese medicine can reduce hs-CRP by 52%. The set α = 0.025, β = 0.2, superiority limit value δ = 20%, and the sample size of each group will be calculated as 30 cases [16, 17]. Considering the loss of follow-up, 40 patients with stable coronary heart disease and 160 with four combinations will be selected.

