TCM has been vastly implicated in the prevention and treatment of CHD. In fact, since the development of integrated Chinese and Western medicine, coupled with the gradual deepening of research, TCM has acquired its own advantages in clinical practice enabling achievement of good efficacy. The basic pathogenesis of CHD is deficiency and blood stasis [22]. A treatment therapy for this condition has involved the use of *Salvia miltiorrhiza* injection, a TCM, whose main components are *Salvia miltiorrhiza* and antibalm. According to the relevant studies in modern medicine, *Salvia miltiorrhiza* can enhance cardiac function, improve the strength of myocardial contraction, increase blood supply to the myocardium, expand the blood vessels outside the heart, and generate very good anti-inflammatory effects [14]. In addition, *Salvia miltiorrhiza* injection has been found to promote blood circulation and remove blood stasis. Studies have further reported that static dripping of *Salvia miltiorrhiza* injection can significantly reduce inflammatory factors in patients with acute coronary syndrome [16], while in patients with acute myocardial infarction, its intravenous injection can reduce the level of hs-CRP and relieve chest tightness and pain [17]. Similarly, astragalus injection has been reported to increase myocardial contractility, with good protective effects on myocardial cells. Consequently, it has been found to effectively improve the cardiovascular function of patients. The drug can also strengthen the phagocytic function of macrophages, improve conversion rate of T cells, promote synthesis of interferon, and improve activity of interleukin. Furthermore, it affects immune regulation, antiviral replication, inhibits allergens, and bacteriostasis. Reports have shown that ulinastatin combined with astragalus injection generates good clinical effects on inflammatory reactions after PCI, which can reduce the expression levels of inflammatory factors in patients and reduce the myocardial injury caused by ischemia and reperfusion, which has important clinical application value [23].

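### The 30 per group does not follow from the printed inputs: the 20% superiority limit equals the whole expected difference, and no SD is given, so the 80% power cannot be verified

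*Protocol article*

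**What the plan says.** The Sample size section of the protocol article takes "hs-CRP as the main effect index". Its effect assumptions are that "Conventional Western medicine treatment can reduce hs-CRP by 32" per cent and that "it is estimated that Chinese medicine can reduce hs-CRP by 52" per cent. The error rates are given as "The set α = 0.025, β = 0.2", without saying whether α is one- or two-sided. The section then states the "superiority limit value δ = 20%, and the sample size of each group will be calculated as 30 cases", citing references 16 and 17. Allowing for loss to follow-up, it recruits 40 per group, 160 in four groups. It prints no SD and no formula.

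The Statistical analysis section plans two-sample t-tests for quantitative data. It adds "All statistical tests will be two-sided with" a significance threshold of 0.05 and mentions no margin.

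The Inclusion criteria require "patients with SCAD treated with any combination of cardiac-related drugs for > 3 months before enrollment".

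**The concern.** A superiority limit is ordinarily a margin that the true difference must exceed. Here it is set equal to the difference the trial expects, which leaves nothing to detect. Read as written, the inputs cannot give 30 or any other number. The planned tests are of no difference, so if the 20% really is a margin, the trial would be sized for one null hypothesis and analysed against another.

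hs-CRP is the only variable used to size the trial, so the 80% power claim rests entirely on this paragraph. If it is unsupported, readers do not know what difference 30 to 40 patients per group can reliably show.

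A second question is whether the 32% and 52% suit the patients enrolled. They have stable disease and have already taken cardiac drugs for more than three months, so a further 32% fall on conventional treatment needs a basis.

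**Working it through.** **Inputs.** All are from the Sample size section unless noted: control reduction 32%; active reduction 52%; Δ = 52 − 32 = 20 points; δ = 20%; α = 0.025; β = 0.2; 30 per group before loss, 40 after. The tests are two-sided at 0.05 (Statistical analysis section). One-sided 0.025 and two-sided 0.05 share the critical value 1.960. For 80% power, z = 0.842, and 1.960 + 0.842 = 2.802.

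**1. The plan's figure as written (superiority by a margin).**
n per group = 2.802² × V / (Δ − δ)², where V is the sum of the two arm variances. With Δ − δ = 20 − 20 = 0 the denominator is zero, so no finite n exists. At a true difference equal to the margin, the test rejects with probability α (2.5% if one-sided) at any n. The figure of 30 is not reproduced.

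**2. 20 points as the difference to detect in mean percent reduction.**
n = 2 × SD² × 2.802² / 20². Solving for the SD:
- n = 30: SD = 20 / (2.802 × √(2/30)) = 27.6 points; 27.2 with the t distribution.
- n = 40: SD = 20 / (2.802 × √(2/40)) = 31.9 points; 31.5 with the t distribution.
- If α = 0.025 is two-sided, 30 per group needs an SD of about 25.1 points (normal approximation).

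The SDs below are assumptions, because the article gives none. Power is for a two-sided 0.05 t-test and a 20-point difference:

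| Assumed SD (points) | Power, 30 per group | Power, 40 per group |
|---|---|---|
| 30 | 72% | 84% |
| 40 | 48% | 60% |
| 50 | 33% | 42% |

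By the normal formula, the n per group for 80% power is 16 at SD 20, 36 at SD 30, 63 at SD 40 and 99 at SD 50. So 30 can be more or less than enough, depending on a figure that is not printed.

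**3. Percentages as responder rates, no margin.**
n = [1.960 × √(2 × 0.42 × 0.58) + 0.842 × √(0.32 × 0.68 + 0.52 × 0.48)]² / 0.20² = [1.960 × 0.698 + 0.842 × 0.684]² / 0.04 ≈ 94.4, so 95 per group. Power would be 34.5% at 30 per group and 44.0% at 40. At two-sided 0.025 the requirement is 115.

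**4. A possible origin of 30.** Adding the margin instead of subtracting it gives a distance of 40 points. On the rates scale this needs 23–24 per group at one-sided 0.025 and 28–29 at two-sided 0.025. It comes close to 30, but it is a non-inferiority calculation and contradicts the superiority aim, so it does not validate the figure.

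**5. Inflation for loss.** 30 / (1 − 0.25) = 40 and 4 × 40 = 160. This part is consistent, with an implied loss of 25%.

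**6. Source of the inputs.** References 16 and 17 are cited for the calculation. The Discussion describes 16 as evidence in acute coronary syndrome and 17 as evidence in acute myocardial infarction. The trial enrols stable, already treated patients, and its Exclusion criteria rule out acute coronary syndrome even after stabilization.

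**The case against.** The best defence is that the 20% is a mislabelled difference to detect. It equals 52 − 32 exactly, the wording elsewhere in the article is loose, and on this reading the planned test of no difference is the matching one. One-sided 0.025 then agrees with two-sided 0.05, and 30 per group is adequate if the SD is about 27 points. The SD may stand in the full protocol or in the cited references. The trial also recruits 40 per group, and last values of dropouts with valid data are carried forward, so the analysed number may exceed 30. All of this is fair. It means that 30 has not been shown to be too small. It does not rescue the printed paragraph, which calls the 20% a superiority limit. An unseen SD would not remove that conflict.

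A reader might go further in three ways that the documents do not support:
- **That 95 per group is the required size.** This holds only for responder rates. The text describes the size of a fall in a continuous marker, defines no responder, and plans t-tests for quantitative data.
- **That no reading gives 80% power.** The mean-reduction reading does, at an SD of about 27 points with 30 per group or 31.5 with 40.
- **That the 32% and 52% were taken from acute patients.** The references follow the sample-size figure. The article attributes the 32% to clinical conditions and calls the 52% an estimate. The Discussion also cites reference 16 for chronic intimal inflammation. The origin is unknown, which is a reason to ask for it.

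**Conclusion.** The point holds as an error in the stated calculation. As written, the margin equals the expected difference, so no finite n exists and power at the assumed effect is α (2.5% if one-sided). On the more natural reading, a 20-point difference in mean percent reduction, the stated 80% power is right only if the SD is at most about 27 points with 30 analysed per group, or 31.5 with 40. Across assumed SDs of 30 to 50, power runs from 72% down to 33% at 30 per group and from 84% down to 42% at 40. These figures assume equal SDs in the two arms, a two-sided 0.05 t-test and a true difference of 20 points. The conclusion is that the power cannot be verified from what is printed. It is not that the trial is too small.

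**What to change.** In the Sample size section:
- Delete the 20% superiority limit. State a two-sided 0.05 test of no difference (equal to one-sided 0.025), with 20 points as the difference to detect.
- State the outcome scale (mean percent reduction in hs-CRP, if that is meant) and the SD, taken from a named source or estimated from pooled, arm-blind data already collected.
- Keep N = 160 and restate the power at 30 to 40 per group. Alternatively, give the detectable difference at 80% power: (20/27.2) × SD = 0.735 × SD at 30 per group and (20/31.5) × SD = 0.635 × SD at 40.
- Give the source of the 32% and 52%, and justify them for stable patients already on cardiac drugs for more than three months.

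The cost is protocol wording and, if no published SD is available, one blinded pooled estimate. No extra patients are needed. The downside is that the stated power may become less favourable.
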